**Fig. 2 Fig2:**
[figure not shown]
CESM image of right breast in MLO view. **a** Low-energy image, which is equivalent to FFDM image. **b** Recombined image. The white arrows indicate the suspect mass, which is only visible on the recombined image and not in the low-energy image. The high-energy image is not shown since it is not of clinical value. Histopathological findings showed grade I invasive carcinoma

### Establishment of final diagnosis (the reference standard)

For the control group, final diagnoses of the (recalled) breast lesions can be divided into four categories [3, 5]: (1) simple cysts; (2) superposition densities; (3) solid, benign masses; (4) (invasive) breast cancer or ductal carcinoma in situ (DCIS). The first three groups are defined as benign findings. To ascertain a final diagnosis of (1), targeted US is performed, followed by cyst aspiration and a second FFDM of that breast to confirm that the lesion has disappeared. Final diagnosis of (2) requires a minimum of one special view or DBT, including targeted US. To rule out false negative (FN) findings, 6 and/or 12 months follow-up or breast MRI can be considered. Final diagnosis for categories (3) and (4) is acquired with US-guided or stereotactic tissue sampling. If cancer or DCIS is diagnosed, the subject will have a ”true positive” (TP) finding. In subjects where no breast cancer or DCIS is diagnosed, the follow-up period of 2 years will determine the true disease status. If no interval cancers have been detected and the subject has not been recalled in the subsequent screening round, the case will be considered a ”true negative” (TN).

In the CESM group, diagnoses are acquired slightly differently. For (1), CESM will show an ”eclipse sign” which is pathognomonic for cysts [3]. No further action is needed. For category (2), a negative CESM exam with no suspect lesion on both low-energy and recombined images rules out (pre)malignant lesions due to CESM’s high negative predictive value [3, 5]. To acquire final diagnoses of (3) and (4), CESM and targeted US are performed including tissue sampling for pathological confirmation.

Since most benign recalls are caused by cysts or superposition densities, the investigated intervention will most likely result in fewer additional exams and tissue samplings among these recalls [3, 5]. Moreover, follow-up exams can be omitted, which is more patient-friendly, and hypothetically, more women will attend the subsequent screening round when they are examined with CESM.

A flow chart is presented in Fig. 3, summarizing the study design, the randomization process, and the establishment of the different diagnoses.

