## Background

In the Netherlands, a national breast cancer screening program was introduced in 1990, with full implementation being completed in 1997. All women aged 50–75 years receive an invitation to participate biennially. At mobile screening units, full-field digital mammography (FFDM) is performed. By default, two images are made per breast, one in cranio-caudal (CC) view and one in mediolateral oblique (MLO) view. The images are independently screened for suspicious lesions by two certified screening radiologists. In the case of discrepancy, a third (senior and unblinded) radiologist will make the final decision regarding referral. In the screening recalls, a distinction is made between Breast Imaging Reporting and Data System (BI-RADS) 0 score and BI-RADS 4 or 5 score recalls [1]. Women recalled with a BI-RADS 0 score are directly referred by their general physician (GP) for additional imaging. Women recalled with a BI-RADS 4 or 5 score are first referred by their GP to an outpatient breast clinic, before being directed to a radiology department for additional imaging [2].

Conventional additional imaging may consist of additional (special) FFDM images or digital breast tomosynthesis (DBT), which can be combined with other imaging modalities, such as breast ultrasound (US). Based on the findings during the imaging work-up, tissue sampling might be recommended: either core needle biopsy (CNB), vacuum-assisted biopsy (VAB), or fine-needle aspiration cytology (FNAC). The total work-up in the evaluation of the recalled women can also be extended with breast magnetic resonance imaging (MRI) (e.g., in inconclusive findings) or 6 and/or 12 months follow-up with FFDM, DBT, and/or US.

Approximately six out of ten recalled women from the Dutch breast screening program are not diagnosed with breast cancer [3]. These recalls generate patient distress and anxiety as well as additional doctor visits, medical imaging, and health care costs [3–5]. Also, participation rates for subsequent screening rounds decrease after a recall of women without malignancy [6].

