### Informed consent and randomization protocol

All recalled women announced at one of the participating centers will be contacted for study participation. Written informed consent will be obtained and the first EQ-5D-5 L and STAI questionnaires regarding anxiety and current health state will be completed before any other study procedure is carried out. Participants are also asked for their consent to use their data in possible future studies. See Additional file 1 for the informed consent form in Dutch.

Women will be randomized to undergo standard of care (control arm) or CESM (intervention arm). Minimization with stratification factors will be applied in the computer-generated randomization screening and enrollment application software ALEA (version 3.0.2083.212r; ALEA Clinical, Abcoude, the Netherlands). Randomization will be stratified by the following: predominant reason for recall (mass, calcifications, asymmetry, architectural distortion), recall BI-RADS score (BI-RADS 0 versus BI-RADS 4/5), and study center. Enrollment in the four centers, including the master randomization file, will be overseen by the Study Coordinator. During the inclusion visit, written consent will be conducted and data entry will be done by one of the research team members in each center to execute randomization using ALEA. Should a problem occur in including a patient or randomization, the Study Coordinator must be reached so that he can provide assistance. After allocation, patient and radiologist will be informed about the outcome; hence, they are not blinded. However, the radiologist is blinded for the outcomes between the two groups, since the final diagnosis and pathology are not yet known. The outcome assessors and data analysts are blinded for the judgment of the next screening round by the screening radiologists, since accuracy also depends on the next screening round outcome. Each participant is assigned a trial identification number for anonymization, to analyze the data, and further to be used in publications. In each participant’s hospital patient file a statement will be noted about study participation and the assigned intervention or control group. On request, study participation can be ended during the follow-up phase.

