### Sample size calculation

Prior research showed a specificity of FFDM of 40% in this population [5]. To enable detection of a clinically relevant increase of specificity by 15% (from 40% to 55%), 176 patients without malignant disease per group are required (power 80%, alpha = 5%). The prevalence of malignant lesions in women recalled from the breast screening program is about 30%; thus, 70% have benign lesions. Therefore, a total of 251 women per group (176/0.7) has to be included. To account for 5% loss to follow-up, the final number of patients to be included is 528 (502/0.95). The calculations were done with OpenEpi [20].

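### The true-negative rule turns on not being recalled at the next round instead of on being free of cancer, so benign next-round recalls have no class and women without a next-round exam pass as negatives

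*Protocol article*

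**What the plan says.** The section on the reference standard states: "In subjects where no breast cancer or DCIS is diagnosed, the follow-up period of 2 years will determine the true disease status". It then gives the rule for a true negative: "If no interval cancers have been detected and the subject has not been recalled in the subsequent screening round, the case will be considered a" … The rule does not ask how a next-round recall ended, and it does not require that the woman attended.

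The article also speaks about attendance. The Background reports that "participation rates for subsequent screening rounds decrease after a recall of women without malignancy". The reference-standard section puts forward, as a hypothesis and without a size, that "more women will attend the subsequent screening round when they are examined with CESM". The Background gives the screening ages as 50–75 and says that women "receive an invitation to participate biennially". The Study population section sets no upper age limit of its own.

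The section on consent and randomization says that "The outcome assessors and data analysts are blinded for the judgment of the next screening round by the screening radiologists", and gives the reason: "since accuracy also depends on the next screening round outcome".

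**The concern.** The rule uses recall as a stand-in for disease, and recall is a poor stand-in. The Background puts benign outcomes at about six in ten recalls, and the Sample size section uses 70%. Two groups are affected.

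- **Benign next-round recall.** The woman is free of cancer by every available check, yet she fails the true-negative condition. She is not a true positive either. The text does not say where she goes.
- **No next-round exam.** A non-attender, or a woman past the screening age, cannot be recalled. She meets the condition by default and is checked only for interval cancer.

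This is the reference standard for the primary outcome. Missed cancers are few, so sensitivity and NPV react to small numbers. If attendance is higher after CESM, as the protocol hypothesises, missed cancers are more likely to surface in that arm, and verification differs by arm.

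**Working it through.** **Inputs from the Sample size section.** Specificity 40% vs 55%; 176 women without malignancy per group; 30% malignant, 70% benign; 5% loss to follow-up; power 80%, alpha 5% (taken as two-sided).

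**The plan's own figure.** The pooled two-proportion formula without continuity correction gives 173 per group, close to the stated 176. Power at 176 is 80.7%. 176/0.7 = 251 and 502/0.95 = 528. The sample size reproduces and is not in dispute.

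**Assumptions, not in the document.** Next-round recall of 2–5%. The benign share of 60–70% describes the recalled population and is carried over to the next round. All women attend in steps 1–3. The illustrative sensitivity is 71/75 = 94.7%, where 75 is 251 × 0.3 rounded.

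**Step 1: who is affected.** Under the BI-RADS cutoff (1–3 benign, 4–5 malignant), a cancer-free woman who tests positive is a false positive whatever happens later. Only test-negative women can lose true-negative status:

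- Control: 176 × 0.40 = 70.4
- CESM: 176 × 0.55 = 96.8

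The benign next-round recall rate is 0.02 × 0.6 = 0.012 to 0.05 × 0.7 = 0.035.

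- Control: 70.4 × 0.012 = 0.8 to 70.4 × 0.035 = 2.5 women
- CESM: 96.8 × 0.012 = 1.2 to 96.8 × 0.035 = 3.4 women

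**Step 2: they lose true-negative status but stay in the cancer-free denominator.** Apparent specificity = true specificity × (1 − benign recall rate).

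| Benign recall rate | Control | CESM | Difference | Power at 176 per group |
|---|---|---|---|---|
| 0 | 40.0% | 55.0% | 15.0 points | 80.7% |
| 0.012 | 39.5% | 54.3% | 14.8 points | 79.8% |
| 0.035 | 38.6% | 53.1% | 14.5 points | 78.0% |

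**Step 3: they are counted as false negatives.** Apparent sensitivity = 71 / (75 + women moved).

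- Control: 71/75.8 = 93.6% to 71/77.5 = 91.7%
- CESM: 71/76.2 = 93.2% to 71/78.4 = 90.6%

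CESM loses more, at equal attendance, only because it has more test-negative women.

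**Step 4: unequal attendance.** Let m be the number of missed cancers among 75, s the share of them found only through next-round attendance, and a the attendance. Apparent sensitivity = detected / [detected + m(1 − s) + m·s·a]. Take a true sensitivity of 90–95% in both arms, s of 50–100%, and attendance of 80% vs 90% or 70% vs 90% (control vs CESM; all assumed).

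- Smallest gap (95%, s = 50%, 80% vs 90%): 95.5% vs 95.2%, about 0.2 points
- Largest gap (90%, s = 100%, 70% vs 90%): 92.8% vs 90.9%, about 1.9 points

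Both are false deficits for CESM. Cancer-free test-negatives classed without a next-round exam number 70.4 × 0.2 = 14 vs 96.8 × 0.1 = 10, or 70.4 × 0.3 = 21 vs 10.

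**The case against.** The strongest reply has five parts.

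1. **The text never says that a benign next-round recall is a false negative.** This stands. A reader might infer it, since true-negative status is refused and nothing else is offered. The sensitivity figures in step 3 hold only on that inference. A reader might also apply the recall rate to all 176 cancer-free women, but that overstates the effect, because test-positive women cannot become false negatives.
2. **Non-attenders are not wholly unverified.** This stands: the interval-cancer condition still applies to them. The allowance in the Sample size section, "To account for 5% loss to follow-up, the final number of patients to be included is 528", might cover some of them, but the text does not link the two. Methods for missing reference status may be in the full protocol or SAP, and the flow chart (Fig. 3) is not shown. That excuses missing detail on methods. It does not repair a rule that is stated.
3. **The attendance difference is only hypothesised, and the bias would run against CESM.** Both are correct. It would be conservative for the superiority aim, but it could still distort the comparison behind the article's expectation of similar sensitivity.
4. **Power is hardly touched.** This largely stands. A reader might infer a serious power loss from unverified women, but power falls that way only if they are dropped. The current rule keeps them, and the number affected cannot be derived from the document. Women past the screening age should be balanced by randomization.
5. **The blinding sentence need not conflict with the rule.** A reader might infer that assessors are denied data the rule needs. It can equally mean that the index reading is kept independent of the later result. The text does not say whether assessors know the allocation. The sentence needs clearer wording, no more.

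**Conclusion.** The point holds as a defect in the stated reference standard. Women proven cancer-free after a next-round recall are left without a class, and women without a next-round exam are classed as negative by default. Nothing in the text shown repairs this.

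The size is modest. At 2–5% recall with 60–70% benign, about one to three women per arm are affected. Specificity, the sizing parameter, moves by about 0.5–2 points, and power stays at about 78–80%. Sensitivity and NPV are more exposed: a fall of about 1–4 points in the sensitivity example, on the unstated false-negative reading. Unequal attendance could add up to about 1.9 points against CESM under the assumptions in step 4. Recall and attendance rates are all assumed; the mislabelling itself does not depend on them. The change should be made, but the defect does not undermine the trial.

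**What to change.** - Define non-cancer as no confirmed breast cancer or DCIS up to and including completion of any next-round work-up. A next-round recall that proves benign then counts as non-cancer.
- Do not count women without a next-round exam, whether non-attenders or past the screening age, as verified negatives by default. Treat their disease status as missing, impute it, and show best- and worst-case bounds by arm.
- Report next-round attendance by arm beside the accuracy results.
- Reword the blinding sentence so that those who classify disease status may use the next-round result.

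The cost is wording and a little analysis. Follow-up through the next round is already planned, so no extra visits are needed. Intervals will be slightly wider once unexamined women no longer count as certain negatives. Accuracy is assessed about two years after inclusion and enrollment was still open, so the rule can be settled before outcomes are analysed.

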Prior retrospective studies have shown that for these women contrast-enhanced spectral mammography (CESM) proved to be an adequate problem-solving tool, reducing the number of false positives while maintaining high sensitivity [3, 5]. Hypothetically, the use of CESM as an imaging work-up in women recalled from screening reduces the number of additional imaging exams and follow-up doctor visits, potentially saving health care costs [7]. Especially for women with dense breasts, CESM seems to be of additional value, since these women are more at risk of undergoing additional imaging or follow-up after recall due to the low sensitivity of FFDM [8, 9]. Moreover, Houben et al. showed that occult breast cancers are detected when using CESM in up to 4% of women in this population, increasing overall accuracy [10].

Therefore, we propose a prospective, multicenter, randomized controlled trial, aiming to study whether a work-up using CESM instead of conventional imaging modalities such as FFDM or DBT (which is the current standard of care) for women recalled from screening is a more accurate, more patient-friendly, and more cost-effective strategy.

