### Primary and secondary outcomes

The primary outcome will be the accuracy assessed by diagnostic performance parameters, such as sensitivity, specificity, positive predictive value (PPV), negative predictive value (NPV), receiver operating characteristics (ROC) curve, and area under the curve (AUC). Radiologists will prospectively provide a single BI-RADS classification for each exam, where a BI-RADS score of 1–3 will be considered ”benign” and 4-5 ”malignant”. The final BI-RADS score (BI-RADS 1–5), based on imaging, will be compared with the BI-RADS score given by the screening program. The accuracy assessed by diagnostic performance parameters will be assessed after the next screening round after approximately 2 years.

Secondary outcomes will be quality of life (QoL), days until final diagnosis, cost-effectiveness, and experienced patient anxiety during a follow-up of 18 months. Three validated questionnaires will be presented at six different time points (at study inclusion; after 2 and 4 weeks; and after 6, 12, and 18 months). QoL will be assessed by the Dutch version of the EuroQol five-dimension, five-level (EQ-5D-5 L) questionnaire, including a visual analog scale (EQ-VAS). This questionnaire is a preference-based instrument used to value health states [11]. The Dutch tariff for the EQ-5D-5L questionnaire, as established by Versteegh et al., will be used to calculate utility scores per health state [12]. Then the quality-adjusted life years (QALYs) will be modeled based on these utility scores. Resource use related to diagnostics will be collected during the trial.

Health-related anxiety, both state and trait anxiety, will be measured by the Dutch version of the State Trait Anxiety Inventory (STAI-DY-1 and STAI-DY-2) questionnaires. Each STAI has 20 items and will be rated on a 4-point Likert scale, scoring 20–80 points per STAI. A higher score corresponds to a higher anxiety level [13].

For the QoL and STAI scores, inter- and intra-patient differences over time from baseline will be compared including those between the intervention and control group. The scores will also be compared between the women with a follow-up exam after 6 or 12 months and those without this follow-up. Figure 1 shows the outcomes defined by the five outcome elements described by Saldanha et al. [14].

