## Discussion

We present the rationale and design of the RACER study, which is a multicenter, prospective, randomized controlled trial investigating the work-up after breast cancer screening referral. This design is in accordance with the SPIRIT guidelines (Additional file 2).

Recent studies have consistently shown that CESM is superior to FFDM, even when the latter is combined with targeted US [26–29]. Lobbes et al. showed that in women recalled from screening, the detection of breast cancer was comparable between the two techniques, but specificity almost doubled from 42.0 to 87.7% when using CESM as a work-up tool [3]. In other words, fewer false positive findings were observed, and with the high negative predictive value of 97.1% in this study, there was a high ability to rule out breast cancer if the CESM showed a negative exam. These initial findings were later confirmed by Lalji et al. in 199 new cases, analyzed by a panel of ten different radiologists [5]. In this study, radiologists without any CESM experience (but with extensive experience in reading FFDM exams) performed as well as radiologists with CESM experience. Reading a CESM exam does not require a dedicated learning curve. Radiologists in the participating centers will have different levels of experience in reading CESM exams. However, these works used a retrospective study design. Also, many other studies on CESM are retrospective in nature. Only some studies collect data prospectively, and most have not done so in a randomized controlled trial like the RACER study.

The RACER study has several strengths. First, a direct comparison between CESM and FFDM, both with targeted US allowed, is possible. Until now, some studies have investigated the comparison between CESM versus FFDM plus targeted US [27, 28]. However, in clinical practice, suspicious findings on CESM are further evaluated with US as well. Klang et al. recently showed that in BI-RADS 3 lesions detected on CESM, targeted US could be used to determine the necessity to perform tissue sampling [30]. Although CESM is superior to FFDM plus US, the difference in diagnostic accuracy is expected to increase again when CESM/US is compared with FFDM/US. To the best of our knowledge, this has not been studied before in a prospective study design.

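### The reference standard is written differently by arm, and in the CESM arm a negative index test is allowed to settle the diagnosis, in conflict with the trial-wide 2-year follow-up

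*Protocol article*

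**What the plan says.** In *Establishment of final diagnosis (the reference standard)*, the control paragraph defines four categories and states how each is reached. For a cyst, "targeted US is performed, followed by cyst aspiration and a second FFDM of that breast to confirm that the lesion has disappeared". A superposition density requires at least one special view or DBT together with targeted ultrasound. The same paragraph then states that, where no cancer or DCIS is diagnosed, the 2-year follow-up determines true disease status.

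The CESM paragraph opens by saying that diagnoses are reached somewhat differently. For a cyst, the eclipse sign is sufficient and nothing more is required. For a superposition, "a negative CESM exam with no suspect lesion on both low-energy and recombined images rules out (pre)malignant lesions", and the reason given is the high NPV of CESM. Categories 3 and 4 need tissue sampling in both arms. The 2-year rule is not repeated.

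Three other places speak of the whole trial. The opening of *Methods* sets a 2-year follow-up until the next screening round. *Primary and secondary outcomes* assesses accuracy after that round. *Informed consent and randomization protocol* says that accuracy depends on the outcome of that round.

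NPV is one of the primary outcome parameters. On the secondary side, "Secondary outcomes will be quality of life (QoL), days until final diagnosis, cost-effectiveness, and experienced patient anxiety", and the abstract adds the number of additional diagnostic exams.

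**The concern.** A reference standard should be independent of the test under study and the same in both arms. Here the section that defines truth lets the index test supply its own final diagnosis for two benign categories, and justifies this by an NPV that the trial is meant to estimate. An analyst following that section would count a cancer missed by CESM as a true negative. CESM sensitivity and NPV would then be too high, and these measures carry the plan's expectation of higher specificity at similar sensitivity.

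The wording also reaches the secondary outcomes. If a CESM diagnosis is final at the first exam while a control diagnosis is final only after further confirmation, days until final diagnosis ends at a different kind of event in each arm. Moreover, *The control group: usual care with conventional breast imaging* leaves DBT and ultrasound to the radiologist's judgment, whereas the reference-standard section makes some of these steps a requirement.

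**Working it through.** **1. The plan's own figure.** Inputs from *Sample size calculation*: specificity 40% against 55%, power 80%, alpha 5% (two-sided assumed, since sidedness is not stated), equal groups. With mean proportion 0.475:

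n = [1.96·√(2·0.475·0.525) + 0.8416·√(0.40·0.60 + 0.55·0.45)]² / 0.15² = (1.384 + 0.588)² / 0.0225 ≈ 173 per group.

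The plan has 176, which is within 2% and gives 80.7% power. Then 176/0.7 = 251.4 and 502/0.95 = 528.4, as stated. A common reference standard would not change these numbers.

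**2. The rules side by side.**

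| Category | Control arm | CESM arm |
|---|---|---|
| Cyst | ultrasound, aspiration, second FFDM | eclipse sign on CESM alone |
| Superposition | special view or DBT, plus ultrasound | negative CESM alone |
| Benign solid mass; cancer or DCIS | tissue sampling | tissue sampling |
| No cancer diagnosed | 2-year follow-up decides | not stated here; implied elsewhere |

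**3. Worst case for CESM.** Assume that every test-negative woman is verified only by her own CESM. Inputs: 251 women; 30% prevalence, so 75.3 with and 175.7 without cancer; and, from the retrospective study cited in the *Discussion*, "with the high negative predictive value of 97.1% in this study". FN = TN × (1 − NPV)/NPV.

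- Specificity 55% (design value): TN = 175.7 × 0.55 = 96.6; FN = 96.6 × 0.029/0.971 = 2.9. True sensitivity = (75.3 − 2.9)/75.3 = 96.2%. With the 2.9 moved to true negatives, sensitivity and NPV both become 100%. Apparent specificity = (96.6 + 2.9)/(175.7 + 2.9) = 55.7%.
- Specificity 87.7% (same retrospective study): TN = 154.1; FN = 4.6; true sensitivity = (75.3 − 4.6)/75.3 = 93.9%, reported as 100%. Specificity moves from 87.7% to 88.0%.

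**4. Range.** At 55% specificity, with NPV assumed between 95% and 99%, the sensitivity gain runs from 6.8 down to 1.3 points and the specificity gain from 1.3 down to 0.3 points. If follow-up finds half of the 2.9 missed cancers (assumption), apparent sensitivity is (75.3 − 2.9)/(75.3 − 1.45) = 98.0% against 96.2%, a gain of just under 2 points.

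**5. The powered comparison.** With 55.7% in place of 55.0%, nominal power at 176 per group goes from 80.7% to 84.3%. With no true difference (both 40%), apparent CESM specificity is 40.7% and the type I error about 5.2%.

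**6. The control arm.** The *Background* says that "occult breast cancers are detected when using CESM in up to 4% of women in this population", and the *Discussion* gives 3–4%. By randomisation a similar share is expected among controls: 251 × 0.03 = 7.5 to 251 × 0.04 = 10.0 women. Those that do not surface within 2 years count as non-cancers. If none is found at work-up or later, and they lie within the 75.3, control sensitivity is overstated by at most 7.5/75.3 = 10 to 10.0/75.3 = 13 points. If they come on top of the 75.3, the upper figure is 10.0/85.3 = 12 points. This bias favours the control arm, and a common reference standard does not remove it.

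**The case against.** A reader might infer that a negative CESM is the only proof of no cancer in the primary analysis. The documents do not support that. Three sections tie accuracy to 2-year follow-up or the next screening round with no restriction by arm. The four categories and the true-positive rule also stand only in the control paragraph, yet the CESM paragraph uses the category numbers, so that paragraph probably carries definitions for the whole trial. The flow chart summarising the diagnoses is not shown. A common rule is therefore likely to be what is meant. This part of the objection stands, and it makes the figures in step 3 upper bounds. They are upper bounds for a second reason: benign solid masses rated BI-RADS 1–3 are to be sampled, so not every test-negative is self-verified.

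A reader might also infer that the differences in exams and days are artefacts of the definitions. That too goes further than the text allows. The trial compares work-up strategies, and fewer confirmatory exams is the stated mechanism, so much of the difference is the effect of interest. Nothing in the document identifies exams done only to satisfy the reference standard, and removing any would discard real resource use.

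Finally, an article may leave the exact end event for days until diagnosis to the full protocol. But this article does state how a final diagnosis is reached, and states it differently by arm. The conflict is on the page.

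**Conclusion.** The point holds as a conflict in the text with a bounded consequence. The section that defines truth gives an arm-specific rule that, followed literally, is incorporation bias in CESM sensitivity and NPV; other sections imply a common rule. In the worst case sensitivity is inflated by 3.8 points at the design specificity and 6.1 points at 87.7%, and NPV becomes 100%. These sizes rest on a retrospective NPV of 97.1%, 30% prevalence and no effective follow-up, and they fall as follow-up is applied. The powered specificity comparison is not threatened, and a claim that it is would not be supported.

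Some differential verification would remain even under a common rule. The reference-standard section itself expects follow-up exams to be omitted after CESM and, as a hypothesis, expects more CESM women to attend the next round. Because the matter defines disease status for the primary outcome, it should be settled before analysis.

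**What to change.** 1. State that for all accuracy analyses one reference standard applies to both arms: histology if tissue was sampled, otherwise cancer status over the 2-year follow-up. Add that an eclipse sign or a negative CESM never counts as the reference.
2. Define days until final diagnosis by the same event in both arms, for example the issue of the conclusive final BI-RADS or pathology report.
3. Reconcile the control-group section, which leaves further imaging to the radiologist's judgment, with the confirmatory steps required in the reference-standard section.
4. Report, by intention to treat and per randomised woman, the cancers detected at work-up and the BI-RADS 4–5 results without cancer. The denominators do not depend on verification, although the numerator of the second still needs verified status. These counts help because verification and next-round attendance may differ by arm, and because occult control cancers that do not surface stay classed as non-cancers.
5. Keep all exams in the exam counts.

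The cost is wording and two extra tables from data already collected. Sample size and patient care are unchanged by items 1, 2, 4 and 5; item 3 asks only that the two sections agree.
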